## Abstract

**Background:**  There is some evidence that electroencephalography guidance of general anesthesia can decrease postoperative delirium after non-cardiac surgery.  There is limited evidence in this regard for cardiac surgery.  A suppressed electroencephalogram pattern, occurring with deep anesthesia, is associated with increased incidence of postoperative delirium (POD) and death.  However, it is not yet clear whether this electroencephalographic pattern reflects an underlying vulnerability associated with increased incidence of delirium and mortality, or whether it is a modifiable risk factor for these adverse outcomes.

**Methods:**  The
**E**lectroe
**n**cephalography
**G**uidance of
**A**nesthesia to Alleviate
**Ge**riatric
**S**yndromes (
**ENGAGES-Canada**) is an ongoing pragmatic 1200 patient trial at four Canadian sites.  The study compares the effect of two anesthetic management approaches on the incidence of POD after cardiac surgery.  One approach is based on current standard anesthetic practice and the other on electroencephalography guidance to reduce POD. In the guided arm, clinicians are encouraged to decrease anesthetic administration, primarily if there is electroencephalogram suppression and secondarily if the EEG index is lower than the manufacturers recommended value (bispectral index (BIS) or WAVcns below 40 or Patient State Index below 25).  The aim in the guided group is to administer the minimum concentration of anesthetic considered safe for individual patients.  The primary outcome of the study is the incidence of POD, detected using the confusion assessment method or the confusion assessment method for the intensive care unit; coupled with structured delirium chart review.  Secondary outcomes include unexpected intraoperative movement, awareness, length of intensive care unit and hospital stay, delirium severity and duration, quality of life, falls, and predictors and outcomes of perioperative distress and dissociation.

**Discussion:**  The ENGAGES-Canada trial will help to clarify whether or not using the electroencephalogram to guide anesthetic administration during cardiac surgery decreases the incidence, severity, and duration of POD.

**Registration: **ClinicalTrials.gov (
NCT02692300) 26/02/2016

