## Background

### Delirium and cardiac surgery

Postoperative delirium (POD) is an acute and typically reversible syndrome, characterized by a fluctuating level of consciousness and disturbances in attention and cognition
^
1
^. Patients undergoing cardiac surgery are at especially high risk of developing POD
^
2–
9
^. The incidence of POD after cardiac surgery is estimated to be between 20% and 70% depending on the population studied and the methods used to assess delirium
^
2–
9
^. Delirium has been described either as hyperactive or hypoactive, the latter being more difficult to diagnose in the clinical setting than the former
^
1
^. As one of the most common complications after cardiac surgery in older adults, POD is associated with prolonged length of hospital and intensive care unit (ICU) stay, increased morbidity and mortality, functional and cognitive decline, and is often associated with placement in long-term care facility
^
6,
7,
10
^.

Several non-modifiable risk factors at the time of surgery are associated with POD including age 60 years and older, preexisting cognitive impairment, psychiatric comorbidities, and low baseline regional cerebral oxygen saturation
^
8,
9,
11–
13
^. Possible precipitating risk factors specific to cardiac surgery include the type of cardiac surgery, cardiopulmonary bypass time, and the number of blood product transfusions
^
7,
9
^. The identification of potentially modifiable perioperative risk factors, for example relating to the conduct of general anesthesia for cardiac surgery
^
7
^, could positively impact this major health issue.

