### Perioperative period (up until discharge)

Delirium and pain are assessed postoperatively in the afternoon/evening while patients are in the hospital. Daily delirium assessments collected specifically for the ENGAGES-Canada study are entered into the Washington University School of Medicine Research Electronic Data Capture (REDCap)
^
40
^ database. EEG data, including BIS values, WAVcns, PSi values, and duration of EEG burst suppression are collected in both the guided as well as in the usual care group. In the usual care group, anesthesiologists are blinded to EEG data
^
23,
41
^. Perioperative data, including the repeated measures data, are saved for analysis from the intraoperative electronic data capture. As part of the routine data collection, we obtain for each patient a detailed medical history, surgical history, specific risk factors, medications, Blessed Dementia rating scale, screening for sleep apnea, laboratory values, medications during surgery, physiological readings, and parameters from the postoperative recovery period. At the time of discharge, patients will also complete a measure of immediate stress reactions (13-item Peritraumatic Distress Inventory; PDI) and peritraumatic dissociation (10-item Peritraumatic Dissociative Experiences Questionnaire; PDEQ) in the perioperative period, which have been found to be strong predictors of incident psychiatric disorders immediately following the stressful experience. Furthermore, they will complete an adapted 4-item PHQ-4 concerning more general anxiety and depressive symptoms, specifically during the perioperative period. These tests take patients approximately 5 minutes in addition to their CAM long form assessment (10 minutes).

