### Sample size calculation statistical analyses

Based on previous studies in cardiac surgery patients, we conservatively estimated a delirium incidence in the control group of 25%
^
2–
9
^ and based on meta-analyses of randomized trials we estimated a relative reduction in delirium with guidance of anesthesia based on EEG waveform of more than one-third
^
3,
7,
24
^. Assuming a two-sided alpha <0.05 and 1200 patients, we estimated >90% power to be able to detect an absolute decrease in the incidence of delirium of 8%
^
27
^. With a more stringent two-sided alpha <0.005, we estimated >70% power. We anticipate that most patients will be available for primary outcome ascertainment (i.e. incident postoperative delirium assessment). Continuous variables will be presented as mean (SD) or median (interquartile range [IQR]), depending on their distributions. Chi-square or Fisher’s exact tests will be used for comparisons of discrete data. Unpaired Student’s t or Mann–Whitney U tests will be used for comparisons of continuous data, depending on their distributions. Confidence intervals for median differences will be calculated using Hodges-Lehmann estimates, and for differences between proportions we will use Newcombe’s method with continuity correction
^
53
^. For the primary outcome, the proportion of patients with incident postoperative delirium will be compared between the two study groups. We will conduct three post-hoc sensitivity analyses to assess whether improved clinician fidelity to the guided protocol might alter the primary outcome. Within the guided group 25% of cases will be excluded with the (1) longest cumulative electroencephalogram suppression time; (2) longest cumulative time with BIS, WAVcns <40 or PSi <25; and (3) highest median volatile anesthetic concentrations. To compare time to delirium onset between groups, we will construct Kaplan-Meier curves for each group and conduct a log-rank test. We will perform a covariate adjustment including likely risk factors for delirium (including age, sex, history of depression, history of delirium, AD* Test, Short Blessed Test, comorbidity index, and study center) using two methods: (1) logistic regression and (2) standardized estimator combined with bootstrapped 95% confidence intervals (CIs)
^
54
^. We will compare delirium incidence between groups, segregated by Charlson Comorbidity Index categories
^
55

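### The three fidelity analyses trim 25% of the guided arm only, so the suppression-time version is biased towards benefit if suppression marks vulnerability

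*Protocol article*

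**What the plan says.** The section on sample size and statistical analyses announces three sensitivity analyses, labelled post-hoc, that ask whether better clinician fidelity would change the primary result. The rule is "Within the guided group 25% of cases will be excluded with the (1) longest cumulative electroencephalogram suppression time". The second analysis drops the quarter with the longest time below the index threshold, and the third drops the quarter with the highest median volatile concentration. No matching exclusion is given for usual care.

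On what suppression means, the Abstract says "it is not yet clear whether this electroencephalographic pattern reflects an underlying vulnerability associated with increased incidence of delirium" and death, or is instead a modifiable risk factor. The Background section on EEG-guided management adds that cumulative suppression is associated with delirium without clear evidence of causality, and that age and comorbidity may raise the risk of burst suppression.

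The data for a symmetric rule exist. Under the perioperative data collection, index values and "duration of EEG burst suppression are collected in both the guided as well as in the usual care group".

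The main comparison is by intention to treat. P<0.05 is to be read as suggestive and P<0.005 as more compelling.

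**The concern.** The trimming variables are measured after randomisation, and the rule is applied to one arm. A guided patient may have long suppression because the clinician did not follow the protocol, or because the patient's brain suppresses easily at modest doses. The rule cannot tell these apart. If the second explanation matters, the rule removes higher-risk patients from the guided arm and leaves their counterparts in usual care. The comparison is then no longer between randomised groups.

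The stake is interpretation. The article's limitations stress that guidance works only if anesthesiologists adhere to it. If the primary result were null, a favourable trimmed analysis could easily be taken as evidence that guidance works when followed. The two P-value thresholds are stated without an exception for these analyses.

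**Working it through.** **Inputs from the article.** Control incidence: "we conservatively estimated a delirium incidence in the control group of 25" per cent. Planned effect: "an absolute decrease in the incidence of delirium of 8" percentage points, so 25% against 17%. Allocation is 1:1, so 600 per arm. Trimming leaves 0.75 × 600 = 450 guided patients.

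**Input assumed.** The risk ratio RR for delirium in the top quarter of suppression time against the other three quarters. The article gives no value, so a range is shown.

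**The plan's own figures first.** The article states: "Assuming a two-sided alpha <0.05 and 1200 patients, we estimated >90% power", and "With a more stringent two-sided alpha <0.005, we estimated >70% power". A two-proportion calculation with 600 per arm and 25% against 17% gives 92.6% and 72.5%. Both reproduce.

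**Artefact under no treatment effect.** Both arms have 25% delirium. Let r be the risk in the retained three quarters and RR × r the risk in the removed quarter:

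0.25 × RR × r + 0.75 × r = 0.25, so r = 0.25 / (0.75 + 0.25 × RR).

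The expected z is (0.25 − r) / √(0.25 × 0.75/600 + r(1 − r)/450). The chance of a false benefit is P(Z > 1.960 − z) at two-sided 0.05 and P(Z > 2.807 − z) at two-sided 0.005.

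Example, RR = 2: r = 0.25/1.25 = 0.200; difference 0.050; standard error √(0.0003125 + 0.0003556) = 0.0258; z = 1.93; false benefit 49% at 0.05 and 19% at 0.005.

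| Assumed RR | Retained guided rate | Spurious difference (points) | False benefit at 0.05 | False benefit at 0.005 |
|---|---|---|---|---|
| 1 | 25.0% | 0 | 2.5% | 0.25% |
| 1.25 | 23.5% | 1.5 | 8% | 1% |
| 1.5 | 22.2% | 2.8 | 18% | 4% |
| 2 | 20.0% | 5.0 | 49% | 19% |
| 2.5 | 18.2% | 6.8 | 77% | 45% |

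**Second scale as a check.** With an assumed odds ratio for the top quarter against the rest and a pooled z test, odds ratios of 1.5, 2, 3 and 4 give 2.0, 3.5, 5.6 and 7.2 points. False benefit at 0.05 is 11%, 26%, 58% and 80%.

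**Simulation.** A continuous risk marker, no treatment effect, 4000 trials per setting. With odds ratios of 1.22, 1.49, 1.82 and 2.23 per SD of the marker, one-arm trimming gives mean differences of 1.5, 3.4, 5.0 and 6.4 points and false benefit at 0.05 in 9%, 25%, 48% and 71% of trials. Trimming the top quarter of both arms gives −0.1 to 0.1 points and 2.3% to 3.0%, against a nominal 2.5%. That result holds because the simulated marker–risk relation is the same in both arms.

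**The second and third markers.** The article links a low index and a higher anesthetic concentration to burst suppression, not directly to delirium. For volatile concentration even the sign is open: vulnerable patients may be given less, in which case trimming the highest values could remove lower-risk patients. No size is computed for these two.

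**The case against.** The strongest reply is that these are sensitivity analyses. Table 1 lists sensitivity analyses among the other exploratory outcomes, the primary comparison is by intention to treat, and nothing in the article says a trimmed result could override it. This stands, and it limits the weight of the point.

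Four stronger readings are tempting, and the article does not support them.

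- A reader might infer that all three analyses will show a benefit even if guidance does nothing. Only suppression is linked directly to delirium, and whether it marks vulnerability is described as unresolved. For the first analysis the bias is conditional on that, and it is a bias in expectation: at RR 1.25 a false significant benefit arises in about 8% of trials.
- A reader might infer that long operations drive the selection, because the Background lists "cardiopulmonary bypass time, and the number of blood product transfusions" among possible precipitating factors for delirium. The article does not say that bypass time lengthens suppression, so this route is plausible but undocumented.
- Quoting only the 0.05 results would overstate the risk under the trial's own evidence rule. At 0.005 the rates for RR 1.5 to 2.5 fall to about 4% to 45%.
- Trimming both arms might look like a complete cure. It is unbiased only under stated assumptions. The article reports less suppression under guidance, so the retained groups need not be comparable, and the contrast is not clearly a fidelity effect.

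The post-hoc label, and whether cumulative time should be scaled by duration, are matters of wording or preference and are not part of this point. What survives the reply is that none of the three comparisons isolates clinician fidelity.

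**Conclusion.** The point holds in a limited form. Excluding a quarter of one arm on post-randomisation variables breaks the randomised comparison. If suppression marks vulnerability, the first analysis is biased towards benefit under no effect, by about 1.5 to 6.8 points for assumed risk ratios of 1.25 to 2.5, against a planned effect of 8 points. False benefit at two-sided 0.05 runs from about 8% to 77%. These sizes rest on the assumed association and on 25% delirium in both arms. If the marker is unrelated to risk, the bias is zero.

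The second and third analyses have the same asymmetry, with bias of uncertain size or direction. The primary analysis is untouched, so this is a correction worth making to exploratory analyses, not a flaw that threatens the trial's main conclusion.

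**What to change.** Do not compare a trimmed guided arm with an untrimmed usual-care arm. Use one of the following, and state its assumption.

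1. **Principal-score weighting.** In the guided arm, model the probability of falling in the retained 75% from baseline covariates. The covariates already listed for the adjusted analysis are a natural start. Weight usual-care patients by that predicted probability. Assumption: the measured baseline predictors are sufficient.
2. **The same exclusion within each arm.** Remove the top 25% of each arm on the same marker, with covariate adjustment, using the data stored for both arms. Assumption: rank preservation and an equal marker–risk relation across arms.

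Add one sentence stating that these exploratory analyses cannot support a claim of benefit if the primary result is null.

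The cost is a change of analysis wording, with no new EEG data collection. The downside is slightly lower precision and reliance on assumptions that the data cannot fully test.

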### Randomization and blinding

Computer-generated assignment at the patient level is used for randomization. Patients who are eligible, and have given informed consent, are randomized to either usual care or to the protocol for guided anesthesia according to the EEG. A one to one ratio of randomization of the patients between usual care and the protocol for EEG-guidance is used. Within the research team, members are trained to enroll participants and assign the randomization between the usual care or the protocol for EEG-guidance. Anesthesiologists and their team learn of the group assignment after the patient is brought into the operating room; an opaque, sequentially numbered, sealed envelope is opened to reveal the study group. The randomization sequence is generated by the data analysis center. The anesthesiologist and the team caring for the patient intraoperatively are not blinded to the group assignment. The patients and family members are not aware of the group assignment. The research team members who are in charge of the assessment of delirium postoperatively remain blinded to the group assignment. Chart reviews are conducted by individuals blinded to the group assignment and blinded to the outcome of the postoperative delirium assessments
^
29,
30
^. Predictability of the randomization sequence is minimized by recording in a separate document, unavailable to the members of the research team who enroll participants and assign groups, the details of patients who have already been randomized.

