## Data collection

### Preoperative

Preoperative assessments are performed in the Pre-Anesthesia Clinic or hospital ward. These include demographic information and medical history, assessment of preoperative quality of life, psychiatric symptoms (i.e., anxiety, depression, alcohol use, trauma history, and posttraumatic stress disorder), objective and subjective cognitive functioning measures
^
35,
36
^, and evaluation of falls’ history. The purpose of the preoperative assessments is to identify cognitive and psychiatric disorders in order to better understand risk factors for postoperative delirium and its sequelae. For example, postoperative delirium has been associated with impaired performance on preoperative cognitive tests
^
37
^, and postoperative delirium predicts persistent postoperative cognitive decline
^
6
^. These known risk factors will be included in covariate analysis for the primary outcome and will be used in exploratory analyses. The following measures were selected for the assessment of cognitive and psychiatric symptoms based on their brevity, frequency of use in medical practice, validity for older adults, and lack of copyright restrictions: (1) 8-item AD8 Dementia Screen
^
38
^, (2) History of Delirium Screen, (3) Short Blessed Test
^
39
^, (4) 3-item Alcohol Use Disorders Identification Test (AUDIT-C), (5) 1-item surgical anxiety visual analogue scale, (6) Trauma History Screen, (7) Posttraumatic Stress Disorder Checklist (PCL-5; past-month PTSD assessment), (8) 4-item Primary Care PTSD Screen (PC-PTSD; lifetime PTSD assessment), (9) 4-item Patient Health Questionnaire (PHQ-4; anxiety and depressive symptoms), (10) 10-item Patient Reported Outcomes Measurement Information System (PROMIS) Global Health (physical and mental health related quality of life), (11) 4-item PROMIS Applied Cognition-Cognitive Concerns, (12) 4-item PROMIS Applied Cognition-Abilities (see extended data
^
32

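### Planned operation type is not among the covariates named for the exploratory adjusted delirium analyses, although the protocol lists it as a possible risk factor; adding it is a minor improvement

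*Protocol article*

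**What the plan says.** Three parts of the protocol article bear on this.

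- **Background, Delirium and cardiac surgery.** After the general risk factors, the text turns to the cardiac setting: "Possible precipitating risk factors specific to cardiac surgery include the type of cardiac surgery, cardiopulmonary bypass time, and the number of blood product transfusions".
- **Sample size calculation statistical analyses.** The primary outcome is compared as proportions between the two groups. A covariate adjustment for likely delirium risk factors is then planned by two methods, logistic regression and a standardized estimator with bootstrapped intervals. The covariates are given as "including age, sex, history of depression, history of delirium, AD* Test, Short Blessed Test, comorbidity index, and study center".
- **Table 1.** Covariate adjustment appears under the other exploratory outcomes, not with the primary outcome.

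On timing, the Overview of the research design restricts entry to elective cardiac surgery with bypass. Randomization and blinding says that the sealed envelope is opened after the patient has reached the operating room. The article does not add operation type to the adjusted analyses elsewhere, and it does not explain its absence.

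**The concern.** The case for testing this intervention in a separate trial is that cardiac surgery carries a particular delirium risk. Yet apart from study center, the named covariates would suit any older surgical population. Of the three cardiac-specific factors in the Background, bypass time and transfusions arise after allocation and are properly absent from the list. The planned operation is different: for an elective case it is settled before the envelope is opened, so adjusting for it is valid.

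If operation type predicts delirium and is left out, two things follow for the adjusted results. Outcome variation that could be explained stays as noise, and a chance difference between arms in operation mix is not accounted for. What is at stake is a little efficiency in a supporting analysis, not the validity of the trial.

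**Working it through.** **1. The plan's own power figure.** Inputs from the sample size section: "we conservatively estimated a delirium incidence in the control group of 25" per cent; "we estimated >90% power to be able to detect an absolute decrease in the incidence of delirium of 8" percentage points, so 25% v 17%; and "Assuming a two-sided alpha <0.05 and 1200 patients". Allocation is 1:1 (Randomization and blinding), so 600 per arm.

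- SE under the alternative: √(0.25×0.75/600 + 0.17×0.83/600) = 0.02340.
- SE under the null, pooled rate 21%: √(2×0.21×0.79/600) = 0.02352.
- Alpha 0.05: Φ[(0.08 − 1.960×0.02352)/0.02340] = 92.6%.
- Alpha 0.005: Φ[(0.08 − 2.807×0.02352)/0.02340] = 72.5%.

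Unpooled variance gives 92.8% and 73.0%; a continuity correction gives 91.6% and 70.1%. All agree with the stated figures, including "With a more stringent two-sided alpha <0.005, we estimated >70% power". The calculation uses no covariates, so nothing below alters it.

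**2. Gain for the standardized risk difference.** The documents give neither the share of higher-risk operations nor their association with delirium. Assumed: a binary planned operation, share q of 20-50%, odds ratio 1.5-3. In each arm the two stratum rates are solved so that they average to 25% or 17%. The explained fraction is

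R² = Σ q(1−q)(p₁−p₀)² / Σ p(1−p), summed over arms,

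and the adjusted SE is the unadjusted SE × √(1−R²).

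Worked case, q = 40% and odds ratio 3:

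- Control strata 16.67% and 37.50%: 0.24×0.2083² = 0.01042.
- Guided strata 10.70% and 26.45%: 0.24×0.1575² = 0.00595.
- R² = 0.01637/(0.1875 + 0.1411) = 4.98%.
- SE = 0.02340×√0.9502 = 0.02281, a fall of 2.5%.

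| q, odds ratio | R² | fall in SE | equivalent extra patients, 1200/(1−R²) − 1200 | power, alpha 0.05 | power, alpha 0.005 |
|---|---|---|---|---|---|
| no covariate | – | – | – | 92.8% | 73.0% |
| 20%, 1.5 | 0.5% | 0.25% | 6 | 92.9% | 73.2% |
| 40%, 2 | 2.0% | 1.0% | 25 | 93.2% | 74.1% |
| 40%, 3 | 5.0% | 2.5% | 63 | 93.9% | 75.8% |

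The first and last covariate rows are the extremes of the grid examined.

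**3. The logistic model.** Unadjusted log odds ratio: ln[(0.17/0.83)/(0.25/0.75)] = −0.4870. SE: √[1/(600×0.1875) + 1/(600×0.1411)] = 0.1439. Power is 92.3% and 71.8%. From the expected information matrix with the covariate added, q = 40% and odds ratio 3 give a log odds ratio of −0.5121 with SE 0.1476, and power of 93.4% and 74.6%. Over the range, the SE rises to 0.1442-0.1476 while power reaches 92.4-93.4% and 72.1-74.6%. The estimate moves away from zero slightly faster than its SE grows, so power improves but the interval does not narrow.

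**4. Limit of these figures.** Steps 2 and 3 compare one covariate with none. The plan already adjusts for eight. If operation type is correlated with comorbidity index or center, the gain beyond those eight is smaller than shown.

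**The case against.** The strongest reply is that nothing here is wrong as written. The covariate list is introduced as illustrative, a final list may sit in a document not shown, and the Background calls operation type only possible where the analysis section speaks of likely risk factors. Baseline cerebral saturation is also named as a risk factor and also unlisted. Most of this stands, and it keeps the point minor. On the last item, the sub-study section says that only some sites measure cerebral saturation routinely, whereas every patient has a planned operation. It also stands that no section says the planned operation is recorded before allocation; that it is knowable follows from elective surgery and the timing of the envelope.

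A reader might infer four stronger things, which the article does not support.

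- **That the plan breaks its own promise.** The Preoperative section says "These known risk factors will be included in covariate analysis for the primary outcome", but the factors meant are the cognitive and psychiatric ones just described there, not surgical ones.
- **That the open list invites adjustment for bypass time or transfusions.** Every named covariate is a baseline or site variable, and transfusions are listed as adverse events. No text proposes adjusting for either.
- **That trial power or the primary result is at risk.** The primary comparison is unadjusted and Table 1 makes the adjustment exploratory. Chance imbalance in operation mix is already allowed for in the unadjusted confidence interval and is not bias.
- **That precision is lost in both methods.** Precision in the sense of a smaller SE is gained only for the standardized estimator; the logistic SE rises.

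**Conclusion.** The point holds as a minor, optional improvement. The covariates named for the exploratory adjusted analyses omit planned operation type, which the protocol itself counts as a possible cardiac-specific risk factor and which, for elective surgery, precedes allocation. It is unnamed rather than formally excluded.

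The assumed share of 20-50% and odds ratio of 1.5-3 are not figures from the documents. Under them the most the standardized estimator could gain over no adjustment is a 2.5% smaller SE, about 1 point of power at alpha 0.05 and about 3 points at alpha 0.005. The logistic model gains slightly in power only. The sample size and the primary analysis need no change.

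**What to change.** Add planned operation type, as booked before randomisation, to both the logistic regression and the standardized estimator, for example as isolated bypass grafting, isolated valve, combined or other. State that all covariates are variables fixed before randomisation, so that the planned operation is used and not the one performed. If the investigators prefer to leave it out, one sentence giving the reason would do.

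The cost is one categorical term in models already planned, and confirmation that the planned operation is captured before allocation for every patient. If it is not captured, it would have to be taken from the surgical booking.

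### Separate arm comparisons within Charlson categories cannot show whether the effect differs by comorbidity, and the article states no heterogeneity test that would

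*Protocol article*

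**What the plan says.** All of the relevant text is in the protocol article, section 'Sample size calculation statistical analyses', unless noted.

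- Subgroup analysis: "We will compare delirium incidence between groups, segregated by Charlson Comorbidity Index categories". The number of categories, their cut-points and their sizes are not given.
- Test: "Chi-square or Fisher’s exact tests will be used for comparisons of discrete data". Delirium yes/no is discrete, so this is the test that would naturally apply within each category.
- Reading of p-values: one rule covers all significance testing. Below 0.05 is suggestive and below 0.005 is more compelling. No separate rule is given for subgroups.
- Intervals: results are to carry 95% CIs, and differences between proportions use Newcombe's method with continuity correction.
- Adjusted model: "We will perform a covariate adjustment including likely risk factors for delirium". The comorbidity index is one of the listed covariates. No product term with treatment is mentioned here or elsewhere in the article.
- Design: "we conservatively estimated a delirium incidence in the control group of 25" per cent; the aim is to "detect an absolute decrease in the incidence of delirium of 8" percentage points. "Assuming a two-sided alpha <0.05 and 1200 patients, we estimated >90% power", and "With a more stringent two-sided alpha <0.005, we estimated >70% power". Under 'Randomization and blinding': "A one to one ratio of randomization of the patients between usual care and the protocol for EEG-guidance is used".

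**The concern.** The reason to split a treatment comparison by comorbidity is to learn whether the effect varies with comorbidity. A set of separate arm comparisons does not test that. A category can miss significance simply because it holds a fraction of the patients, and a result below 0.05 in one category and above it in another is no evidence that the two effects differ. The article goes beyond leaving detail open: it names a subgroup method, and that method does not answer the subgroup question.

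At stake is the reading of one supplementary analysis. If guidance works equally well in everyone, the separate p-values may well disagree with each other. If it works in no one, one category may still look promising by chance. The primary comparison and the sample size are not affected.

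**Working it through.** **Inputs.** From the article: control risk 0.25, guided risk 0.25 − 0.08 = 0.17, 1200 patients at 1:1 (600 per arm), two-sided alpha 0.05 and 0.005. Assumed: two to five Charlson categories with various splits, balanced arms within each category, all patients assessable for delirium, and the design effect true in every category.

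**Formula.** With n per arm and mean risk p̄ = (0.25 + 0.17)/2 = 0.21:

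power = Φ{ [0.08 − z·√(2·0.21·0.79/n)] / √[(0.25·0.75 + 0.17·0.83)/n] } = Φ{ [0.08 − z·√(0.3318/n)] / √(0.3286/n) }

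**1. The plan's own figures, n = 600.**
- Alpha 0.05: (0.08 − 1.96 × 0.02352)/0.02340 = 1.449, power 92.6%.
- Alpha 0.005: (0.08 − 2.807 × 0.02352)/0.02340 = 0.598, power 72.5%.

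Both agree with the stated figures (above 90% and above 70%). With a continuity correction they are 91.6% and 70.1%. The trial's power statement is not in question.

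**2. Power within equal categories, alpha 0.05.**
- Two categories, n = 300: (0.08 − 0.06518)/0.03310 = 0.448, power 0.673.
- Three, n = 200: (0.08 − 0.07983)/0.04053 = 0.004, power 0.502.
- Four, n = 150: (0.08 − 0.09218)/0.04681 = −0.260, power 0.397.

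**3. Chance of a mixed pattern under a uniform effect.** Mixed means at least one category significant and at least one not. Categories are independent, so P(mixed) = 1 − P(all significant) − P(none significant).
- Two: 1 − 0.673² − 0.327² = 0.44.
- Three: 1 − 0.502³ − 0.498³ = 0.75.
- Four: 1 − 0.397⁴ − 0.603⁴ = 0.84.

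| Split of patients (%) | Mixed at 0.05 | Mixed at 0.005 |
|---|---|---|
| 50/50 | 44% | 45% |
| 70/30 | 52% | 51% |
| 80/20 | 62% | 58% |
| 90/10 | 75% | 65% |
| three equal | 75% | 48% |
| 50/30/20 | 78% | 50% |
| 60/30/10 | 83% | 55% |
| four equal | 84% | 44% |
| 40/30/20/10 | 86% | 47% |
| five equal | 86% | 40% |

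If baseline risk rises with comorbidity and the relative risk is a uniform 0.17/0.25 = 0.68, the range at 0.05 with three or four categories is again 75% to 86%.

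**4. Comparison with a heterogeneity test.** Eight of these splits (two to five categories) were simulated 40,000 times each under the uniform 25% v 17% effect. Cochran's Q on the category risk differences, Q = Σ wᵢ(dᵢ − d̄)² against chi-square with k − 1 degrees of freedom, rejected at 0.05 in 5.1% to 5.6% of trials. The simulated mixed-pattern rates (44%, 75% and 84% for two, three and four equal categories) matched step 3.

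**5. No effect at all.** The chance that at least one category reaches p<0.05 is 1 − 0.95ᵏ: 9.8% for two, 14.3% for three, 18.5% for four. At 0.005 it is 1 − 0.995ᵏ: 1.0%, 1.5%, 2.0%.

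**6. The scale of the heterogeneity test matters.** Assume baseline risks of 15% and 40% for illustration.
- A uniform 8-point reduction gives odds ratios (0.07/0.93)/(0.15/0.85) = 0.43 and (0.32/0.68)/(0.40/0.60) = 0.71. A logistic product term could then register a difference although the absolute effect is constant.
- A uniform relative risk of 0.68 gives reductions of 0.32 × 15 = 4.8 and 0.32 × 40 = 12.8 points, so the risk-difference scale is not neutral either.

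**7. What a heterogeneity test could detect.** With two equal categories, the standard error of the difference between two risk differences is √2 × √(0.3286/300) = 0.0468. For 80% power at two-sided 0.05, the two effects must differ by about (1.96 + 0.84) × 0.0468 = 0.131, or 13 points, against an overall design effect of 8.

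**The case against.** The strongest reply is that this is a condensed article. Interaction terms and subgroup cut-points are commonly set out in an SAP, and their absence here is no fault. That stands as far as it goes: a reader might infer that the trial has no interaction test, but the article shows only that none is stated in it. It does not dispose of the point, because the article does state a subgroup method, and it is the stated method that fails to answer the question.

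Second, the sentence on Charlson categories contains no rule for declaring that effects differ, and 95% CIs are already promised. That also stands. Treating the separate comparisons as a contest of p-values is a step the reader would have to take. Nothing in the article says guidance will be recommended or withheld by Charlson category, so the inference that the plan leads to a wrong recommendation for particular patients is not supported.

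Third, a reader might infer that a uniform effect will usually look like a subgroup difference. The documents do not support this as a general statement. The number of categories is not given. With two equal categories the mixed pattern occurs in 44% of trials, and at the 0.005 tier the range is 40% to 65%. These are also probabilities of a p-value pattern, not of a mistaken conclusion.

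Fourth, putting the test only in the planned logistic model would bring its own difficulty, since the odds-ratio scale can show an interaction when the absolute effect is constant. That is correct, and the fix takes account of it.

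**Conclusion.** The point holds in a limited form. The article fixes only separate arm comparisons within Charlson categories, graded by the general p-value rule, and states no heterogeneity test. Under a uniform 25% v 17% effect at 0.05, that approach gives a mixed picture in about 44% of trials with two equal categories, 52% to 75% with the unequal two-way splits tried, and 75% to 86% with three or four. A heterogeneity test signals falsely in about 5%. With no effect, at least one category reaches p<0.05 in 10% to 19% of trials with two to four categories.

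These figures rest on an assumed number and size of categories and on all 1200 patients contributing. The mixed-pattern figures also take the design effect as true. They describe a presentation that invites misreading, not an error the trial is bound to make. The primary analysis and the stated power are sound on this point. The change is worth making because it costs almost nothing.

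**What to change.** Replace the within-category tests with one treatment-by-Charlson heterogeneity test on a scale stated in advance. The risk difference is preferable, because the trial is powered on an absolute reduction. The odds-ratio interaction from the planned logistic model can be given as a supplement. Report the risk difference in each category with the Newcombe 95% CI already planned, without a p-value of its own. Say that a subgroup difference will be claimed only on the heterogeneity test, and give the category cut-points alongside. If the SAP already contains such a test, it is enough to align the article's sentence with it.

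The cost is a sentence or two and one extra analysis; no data collection, sample size or primary analysis changes. The drawback is limited power: as worked out above, even two equal categories would need effects about 13 points apart for 80% power. The plan should say so, and should say that a non-significant heterogeneity test does not show that the effect is the same in all categories.
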